## Abstract

**Background:**

Patients undergoing open abdominal aortic aneurysm (AAA) repair remain at high risk for postoperative complications, particularly when presenting with limited baseline functional capacity. Prehabilitation, encompassing physical, nutritional, and psychological optimization before surgery, may improve outcomes in this population. However, evidence is limited in the context of open AAA repair.

**Objective:**

To evaluate the effectiveness of a multimodal prehabilitation program in reducing the incidence of postoperative complications in patients undergoing open AAA repair.

**Methods:**

This is a multicenter, international, randomized controlled trial. Eligible participants include adults scheduled for elective open AAA surgery. A total of 152 participants will be randomized 1:1 to receive either standard preoperative care or a 6-week multimodal prehabilitation program consisting of supervised exercise training, individualized nutritional support, and psychological counseling. The primary outcome is the rate of postoperative complications as measured by the Comprehensive Complication Index (CCI). Secondary outcomes include length of hospital stay, and readmission rates, changes in functional capacity, health-related quality of life and anxiety & depression. Data will be analyzed on an intention-to-treat basis. The study complies with SPIRIT 2013 guidelines and is registered at ClinicalTrials.gov (NCT05756283).

**Discussion:**

This trial will address a significant evidence gap regarding preoperative optimization in open abdominal aneurysm surgery. Findings will inform best practices for reducing morbidity in this high-risk population and contribute to enhanced recovery strategies in vascular surgery.

**Trial registration:**

[NCT05756283]

## 1. Introduction

### 1.1 Background and rationale

It is estimated that 20000 Canadians are diagnosed yearly with an abdominal aortic aneurysm (AAA) [1]. AAAs are usually asymptomatic until they rupture, which carries an 80–90% overall mortality [2,3]. In order to prevent rupture, AAAs are repaired when they reach a diameter of 5.5 cm in men and 5.0 cm in women [4]. Patients with AAA are highly comorbid, often have poor functional status and are considered high risk for adverse surgical outcomes [5]. AAAs can be repaired either by endovascular repair (EVAR) or open surgical repair. While EVAR may be less invasive, approximately 30–50% of patients are not candidates due to anatomical considerations [6]. In addition, it results in increased reinterventions and may have worse long-term survival [7–14]. Therefore, open repair remains a viable intervention in many patients; unfortunately, it is associated with a 3.6–4.2% mortality, and a morbidity of 30–40% [15–17]. Despite improvements in perioperative care, the rate of complications in open repair has remained relatively stable for the past 10–15 years [16]. In the short term, post-operative complications lead to an increased likelihood of dying in hospital, prolonged hospital stays, slower return to baseline, increased readmission rates, and decreased quality of life. In the long term, they can lead to decreased life expectancy, undermine physical and mental health, decrease patients’ functional status, and possibly threaten their independence [18–20]. Not only do complications affect the patients and their caregivers, but they also result in significant economic burden to the health care system and society as a whole [18–20].

Functional status is an individual’s ability to perform the normal daily activities required to meet basic needs, fulfill usual roles, and maintain health and well-being [21]. It has been shown to be a true measure of perioperative risk, and when functional status is poor, it is associated with worse perioperative outcomes [22–24]. The risk factors leading to poor functional status such as smoking and unhealthy behaviors are common in patients with AAA [25]. As such, individuals with AAA have significantly lower functional status and more comorbidities than aged-matched controls [26]. Fortunately, functional status is a modifiable preoperative risk factor that, if improved before surgery, leads to a decrease in postoperative morbidity [27,28]. The use of the preoperative time to optimize functional status to the goal of improving surgical recovery and perioperative morbidity is called prehabilitation [29–33]. Multimodal prehabilitation (MP) targets the three main pillars of functional status, namely, physical, nutritional, and psychological well-being [34]. Physical exercise has been the main component of most unimodal and multimodal prehabilitation programs with all types proving beneficial, from resistance training, to low, moderate, and high intensity interval training (HIIT) [35–38]. Nutritional status, the second component of MP, is independently associated with postoperative morbidity and mortality [39], and supports optimal gains in exercise-induced functional capacity [40]. Malnourishment exacerbates the catabolic state induced by surgery, limiting healing and surgical recovery [41]. Nutritional interventions are more effective in maintaining lean body mass if instituted before surgery than if commenced after [42,43]. Finally, psychosocial wellbeing and mental health, often overlooked, are an important component of recovery. Undergoing surgery is linked to emotional stress. Several studies have demonstrated the association between anxiety and depression with adverse postoperative outcomes, including increased length of hospital stay, infection, and poor wound healing and increased mortality [44–47]. MP addresses all three elements in one intervention because while important individually, they create a synergistic effect when combined [48]. Several studies have demonstrated that prehabilitation improves functional recovery and facilitates the recovery of daily activities of cancer participants after major surgery [23,49]. Improvements are greater in patients with poor baseline physical fitness, with prehabilitation decreasing overall complications and their severity after major surgery [50]. In high-risk patients undergoing major abdominal oncological surgery, prehabilitation decreased complications by 50% [28]. While there is high-quality evidence that backs up the feasibility and safety of HIIT programs on patients scheduled to undergo elective AAA repair, the evidence supporting prehabilitation’s capacity to reduce complications in AAA surgery is insufficient and heterogenous with no trial using the multimodal approach and most of the trials mixing cohorts of open and endovascular repair [26,51–53]. It seems logical to think that patients undergoing open AAA repair would benefit more from MP as this group clusters a higher incidence of postoperative complications compared to the endovascular repair patients. In conclusion, there is a lack of and a need for, high quality RCTs on multimodal prehabilitation before open AAA repair.

## 2. Objectives

Primary Objective: To investigate the role of multimodal prehabilitation in decreasing postoperative complications measured by the Comprehensive Complication Index (CCI) in patients undergoing open AAA repair.

Secondary Objective(s): To investigate the effects of multimodal prehabilitation on perioperative functional capacity, Health-Related Quality of Life, anxiety and depression, intensive care unit (ICU) stay, length of hospital stay, readmission rates, emergency visits, and cost-effectiveness of such program. The trial will also assess the compliance, fidelity, participant satisfaction and safety of the intervention.

## 3. Methods and analysis

### 3.1 Trial design and ethics

The trial protocol was written following the Standard Protocol Items: Recommendations for Interventional Trials (SPIRIT) guidelines [54]. This is a prospective, international, multicenter, open label, randomized controlled trial with an allocation ratio 1:1 comparing standard of care versus 6 weeks of a multimodal prehabilitation program. The recruitment period started in September 2024 and will last until September 2027. Recruitment of participants will take approximately three years, the follow-up and data collection after recruitment phase will last one year, and results will be analysed within a year of finishing. Both primary endpoint and baseline data will be blindly assessed. Intention-to-treat criteria will be used to define the analysis population; all randomized participants will be included in the analysis according to assigned group. The trial is registered on the Registry of National Institutes of Health ClinicalTrials.gov, a database of privately and publicly funded clinical studies conducted around the world (NCT05756283). The trial will be conducted according to the rules of Good Clinical Practice. The study will be conducted according to the principles of the Declaration of Helsinki and in accordance with the Medical Research Involving Human Subjects Act (WMO) and has been reviewed by the ethics board of McGill University Health Centre MP-37-2023-8983. No datasets were generated or analysed during the current study. All relevant data from this study will be made available upon study completion.

### 3.2 Setting

This trial will be conducted in the following academic tertiary hospitals: McGill University Health Centre (Montreal, Canada), Sir Mortimer B. Davis Jewish General Hospital (Montreal, Canada), Hospital Clínic de Barcelona (Barcelona, Spain) and Dalhousie University affiliated Hospitals (Nova Scotia, Canada).

### 3.3 Eligibility criteria

#### 3.3.1 Inclusion criteria.

Participants older than 50 years of age awaiting elective open AAA repair with AAA diameter ≤6.9 cm. Participants must have the ability to give individual informed consent.

#### 3.3.2 Exclusion criteria.

Participants undergoing thoracic, thoracoabdominal and/or perivisceral AAA repair.Participants with ruptured or symptomatic AAA.Participants with AAA maximal diameter ≥7 cm.Physical inability to exercise: severe osteoarthritis, musculoskeletal or neurological impairment that precludes exercise.Contraindication to exercise: rest systolic blood pressure ≥ 180 mmHg and/or diastolic ≥ 100 mmHg, uncontrolled atrial or ventricular arrythmias or proven exercise induced arrhythmias, unstable angina, unstable or acute heart failure, severe symptomatic valvular stenosis, dynamic left ventricular outflow tract obstruction or other comorbidities that imply clinical instability.Cognitive impairment that would impede understanding of study procedures, informed consent or study questionnaires or the inability to effectively communicate in English/French/Spanish/Catalan.

### 3.4 Study outcomes

#### 3.4.1 Primary outcome.

The primary outcome of this study is the incidence of postoperative complications measured by the Comprehensive Complication Index. The CCI was developed to address some of the limitations of traditional surgical morbidity reporting, such as only reporting the most severe complication or only picking the most common types of complications [55,56]. It provides a continuous score from 0 (no complications) to 100 (death) that integrates the cumulative burden of all complications and their severity. It has been validated in surgical abdominal, urologic, and cardiothoracic patient populations [47,57,58]. It correlates better than any other scale with respect to length of stay, cost/burden to the health care system, readmissions, and disability [59–61].

#### 3.4.2 Secondary outcomes.

Secondary outcome measures will fall into 5 categories:

Healthcare-related: Intraoperative complications, ICU length of stay, hospital length of stay, reintervention, 6-week and 1-year mortality/ readmission/ emergency room visit and prehabilitation cost-effectiveness.Change in functional and aerobic capacity measured by:6-minute walk test: the 6MWT evaluates the ability of an individual to maintain a moderate level of physical activity reflective of the activities of daily living [62]. As daily activity is mostly pursued at a submaximal level, functional walking capacity is a more direct measure of capacity for daily routine. Therefore, it is a useful tool to assess postoperative recovery and return to normal life [63].VO2-peak, VO2-AT, VE/VCO2-AT: Cardiopulmonary Exercise Testing (CPET) is the current gold standard to assess aerobic capacity [64]. It provides an assessment of the integrative exercise responses involving the pulmonary, cardiovascular, hematopoietic, and skeletal muscle systems [64]. VO2 peak, VO2-AT and VE/VCO2-AT are CPET derived variables that predict postoperative morbidity and mortality, as well as indicators of cardiorespiratory fitness.Yale physical activity survey (YPAS): YPAS is a self-reported measure of physical activity, comprising 18 activities evaluated according to the total number of hours done during an average week [65].Patient reported outcomes:Health-related quality of life (SF-36): the SF-36 is the most widely used health-related quality of life measure and has been validated for surgical populations. It incorporates behavioral functioning, subjective wellbeing, and perceptions of health. Two summary scores have been developed: the Physical Component Summary and the Mental Component Summary, standardized to have a mean of 50 and a standard deviation of 10. A higher score on the SF-36 sub-scales or component summary measures indicates a better quality of life. A change of as little as 2 units on the physical component summary has been shown to be the minimum clinically meaningful change; 5 points is often targeted by medical intervention studies, though surgical interventions can have an impact as large as 10 points [66,67]. Data obtained from the SF-36 will be used to calculate the quality adjusted life years using the SF-6D [66].Hospital Anxiety and Depression Scale (HADS): HADS is a reliable instrument for screening clinically significant anxiety and depressive symptoms in medically ill patients [68]. It has also been shown to be a valid measure of their severity [68]. It includes items that assess generalized depression and anxiety, including tension, worry, fear, panic, difficulties in relaxing, and restlessness.Nutritional status outcomesPatient Generated Subjective Global Assessment (PGSGA): the PGSGA is a screening tool used to identify malnutrition and consists of two parts. The first part is the Patient Generated Subjective Global Assessment Short Form which is a widely validated malnutrition screening tool and has been previously used in vascular surgery [69–71]. The second part is completed by a dietitian and includes a physical examination, where fat and muscle stores and fluid status are evaluated, and an assessment of the disease/condition. The global score generates a subjective category rating for nutritional status.Body composition: Weight, BMI, Fat free mass (kg) and body fat mass (%) will be assessed using bioimpedance.Diet: A registered dietitian will assess usual energy and protein intake, including supplements, at baseline and pre-surgery using three-day food records or 24-hour dietary recalls.Study related outcomes:Compliance: compliance to supervised and home-based exercise will be calculated by counting the number of sessions attended by the participant. Home-based exercise compliance will be estimated by counting the number of sessions they logged in an exercise logbook. Compliance to nutrition will be evaluated based on the assessment of dietary changes/goals set by the dietitian. Every week participants will be asked if the nutrition goals set have been met.Fidelity: fidelity to supervised and home-based exercise will be recorded. Supervised exercise fidelity will be measured by recording the watts (for endurance training) and kg (for strength training) at which the participants train during the session (versus expected according to the individualized plan) as well as heart rate and RPE for both breathing and muscular fatigue [72].Satisfaction and acceptability of the intervention: a satisfaction survey enquiring about the different components of the prehabilitation will be given upon completion of the intervention (S1 File).Safety: safety will be assessed by recording the appearance of any adverse event occurring during assessments or intervention. A list of adverse events can be found in S5 File.

### 3.5 Study outline and procedures

The study CONSORT diagram, an overview of the study flow and the measurements taken during the PREHAAAB study can be found in .

**Fig 1 pone.0339473.g001:**
[figure not shown]
SPIRIT participant timeline; Schedule of enrollment, interventions, and assessments. PGSGA: Patient-Generated Subjective Global Assessment; CPET Cardiopulmonary Exercise Testing; 6MWT 6-Minute Walk Test; YPAS Yale Physical Activity Survey; AE Adverse Event; SAE Serious Adverse Event; CCI Comprehensive Complication Index.

**Fig 2 pone.0339473.g002:**
[figure not shown]
Study CONSORT diagram. AAA Abdominal Aortic Aneurysm; CPET Cardiopulmonary Exercise Testing.

**Fig 3 pone.0339473.g003:**
[figure not shown]
Study flow. YPAS Yale Physical Activity Survey; AE Adverse Event; SAE Serious Adverse Event; CCI Comprehensive Complication Index; ER Emergency Room.

#### 3.5.1 Participant screening, recruitment and informed consent (T-1).

In all participating centers, participant selection will begin after a high probability of having open AAA repair is stablished by the perioperative vascular team. Within one week of the decision to go for surgery, a medical research team will screen for health conditions that preclude study participation. The participant will be contacted by a study coordinator who will ask for willingness to participate in the study. The participant will be offered the possibility to participate in the trial and, if the participant agrees, a first baseline appointment (T0) will be scheduled where written and oral information about the trial will be given.

The study coordinator will answer any questions that participants might have and ask if the patient is willing to participate in the trial. The right of a patient to refuse participation without giving reasons will be respected. The patient will remain free to withdraw at any time from the study without consequences for further treatment.

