***Randomization*:** Randomization will be performed after baseline assessment. Participants will be randomized to both arms equally a (1:1 ratio) upon final confirmation of eligibility. A stratified randomization will be performed by site and sex; with block size 2,4 and 6 to ensure unbiased allocation of the patients. Allocation to study group will be revealed using RedCap software to the research team that will carry out the intervention once baseline assessment is completed.

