#### 3.5.6 Surgery and admission (T8).

Perioperative clinical protocols will be followed according to each site’s standard of practice independently of group allocation; [76]. Anesthesia procedures and surgery will be performed by the usual anesthesia and vascular surgery teams of each site. Hospital healthcare providers (nurses, anesthesiologist, vascular surgeons, physiotherapists, etc.) involved in the participants care will be blinded to the study group allocation, unless the participant discloses that information. To avoid that, participants will be advised not to disclose their allocation to healthcare providers. Any intraoperative deviation of the standard course or event will be recorded (S3 File). The use of blood products, as well as the need for high doses of vasopressors intraoperatively will also be recorded (high doses of one vasopressor or the use of two or more vasopressors) in the case report form. Postoperative care will not differ between groups and will follow the standard of practice for each site. Postoperative complications throughout admission will be assessed daily by a physician and will be recorded in the CRF by a research team member. Both team members will be blinded to the study group allocation to avoid bias. The primary outcome of the study, the Comprehensive Complication Index (CCI), will be calculated based on the number and severity of the complications recorded. A description of complications and their severity can be found in the S4 File. Length of ICU stay, need for a reintervention and hospital length of stay will be recorded.

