### 3.6 Statistical analyses

#### 3.6.1 Sample size.

Sample size was calculated for the primary outcome of complications as defined by the CCI. From the literature, the mean CCI ranges from 25–35 after open AAA repair, and their standard deviations are 17–30. We have chosen 30 as the most clinically relevant mean difference for the CCI and standard deviation of 20. Given the inputs, we require a total of 126 patients to achieve standard 80% statistical power and 5% tolerance. After considering a 20% dropout rate, we require 152 patients (76 per group) in this study. Since one interim analysis was planned, a total of 40 patients were needed in each treatment arm at the time of analysis to adequately power the interim analysis based on the type-I error suggested by the O’Brien-Fleming method (a minimum P = 0.0054).

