#### 3.6.2 Primary analysis.

The primary analysis will be conducted by the intent-to-treat approach; differences in CCI scores between MP and the standard-of-care arms will be assessed in 45 days. Descriptive statistics will be performed using means, proportions, medians, standard deviations, and interquartile ranges, as appropriate depending on the nature of the data. We will use Generalized Linear Mixed or Generalized Estimation Equation models to evaluate the impact of the intervention, accounting for between and within group differences. The effect of MP on specific postoperative complications will be analyzed using parametric tests for categorical variables. The effect of MP on functional improvement and quality of life will be analyzed using time interactions with the group after considering the site at a random level. In addition, we will perform the sensitivity analysis based on a per-protocol approach using mixed effects, with study site as the random effect to cross-validate our results. We also plan to perform subgroup analyses of the primary outcome measure, as well as MP adherence on the following groups: study site, sex, and other variables which have previously been shown to impact MP adherence as well as postoperative outcomes after AAA repair, such as age, diabetes, renal failure, and baseline functional status.

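### All randomised participants are promised a primary CCI analysis, but the CCI has no assured source for those who die before admission, are cancelled, or are excluded after an event

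*Protocol article*

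**What the plan says.** All references are to the protocol article.

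- **Analysis set.** Section 3.1: "all randomized participants will be included in the analysis according to assigned group". Section 3.6.2 repeats intention-to-treat for the primary outcome and adds that "differences in CCI scores between MP and the standard-of-care arms will be assessed in 45 days", without saying from when the 45 days run.
- **Timing.** Section 3.5.1 begins selection "after a high probability of having open AAA repair is stablished". Section 3.5.2: "Randomization will be performed after baseline assessment". Sections 3.5.4 and 3.5.5 then put a programme of 6 ± 1 weeks, and possibly a longer wait, before surgery.
- **Source of the CCI.** Section 3.5.6: "Postoperative complications throughout admission will be assessed daily by a physician", and the CCI "will be calculated based on the number and severity of the complications recorded". Section 3.4.1 places death at 100 on the scale.
- **Later follow-up.** Sections 3.5.7 and 3.5.8 time both postoperative visits from discharge. Section 3.5.8 also has hospital records checked for emergency visits, admissions and mortality.
- **Exclusion after an event.** Section 3.7 says that a participant with an event at an assessment or in training is referred and excluded from the study. Section 5.1 names aneurysm rupture and arrhythmia among possible serious adverse events.
- **Allowance for loss.** Section 3.6.1: "After considering a 20% dropout rate, we require 152 patients (76 per group) in this study".

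**The concern.** The primary outcome is collected at a point that a randomised participant may never reach. Weeks pass between randomisation and admission, and this is the period in which the arms are treated differently: one has supervised exercise and more clinical contact, the other has usual care. If a CCI exists only for those admitted, the comparison is conditional on something that happens after randomisation and may depend on the arm.

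The exclusion in section 3.7 sharpens this. The baseline exercise test precedes randomisation, so an exclusion there does no harm to the comparison. The preoperative assessment follows randomisation and is done in both arms. Training also follows randomisation, and the programme is given only to the intervention arm. An exclusion triggered by a training event can therefore fall on one arm alone.

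At stake is whether harm before surgery counts against the intervention or leaves its mean CCI untouched.

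**Working it through.** **Step 1. Follow each kind of participant to a CCI.**

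- *Open repair done:* admitted, so section 3.5.6 supplies a CCI.
- *Switched to endovascular repair:* admitted. Section 3.5.6 does not restrict recording to open repair, so a CCI can exist.
- *Rupture that reaches surgery:* admitted, so a CCI can exist.
- *Death before admission:* no recorded admission. The scale would allow a score of 100, but no section says it will be given.
- *Cancelled or never operated on:* no admission, and no discharge from which to time the later visits.
- *Excluded under section 3.7 after randomisation:* not stated whether follow-up and analysis continue.

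The last three groups have no assured CCI, although section 3.1 includes them.

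**Step 2. The plan's own sample size, to find the effect it corresponds to.** Per arm, n = 2(1.960 + 0.842)² × (SD/difference)², with SD 20, two-sided 5% and 80% power (section 3.6.1 does not state sidedness).

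- Difference 30, as stated: 2 × 7.849 × (20/30)² = 6.98, so 7 per arm and 14 in total. This does not give 126.
- Difference 10: 2 × 7.849 × (20/10)² = 62.8, so 63 per arm and 126 in total. This gives the plan's figure.

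The mismatch between 30 and 10 is a separate matter. Here 10 serves only as the benchmark that 126 implies. The allowance for loss is 152 − 126 = 26, and 26/152 = 17.1%. If 20% of 152 had no CCI, 152 × 0.8 = 121.6 would remain.

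**Step 3. Effect of omitting a preoperative death (illustration).** Inputs: 76 per arm (section 3.6.1); mean CCI near 30, within the 25–35 cited there; number of deaths assumed, because the article gives no rate. With k deaths scored 100 instead of omitted, the arm mean rises by k(100 − 30)/76.

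- k = 1: 70/76 = 0.92 points
- k = 2: 140/76 = 1.84
- k = 3: 210/76 = 2.76, about 28% of a 10-point difference

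If the intervention arm's mean were 20, each death there would count (100 − 20)/76 = 1.05. An operated-only difference of 10 would become 8.95, 7.89 and 6.84 with one, two and three deaths in that arm alone. One death in each arm would change the difference by only (80 − 70)/76 = 0.13.

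**Step 4. What keeping everyone costs in power (illustration).** Assumptions: operated means 30 and 20, SD 20, 76 per arm, the same share q not operated in each arm, survivors without surgery scored 0, no deaths. The difference becomes 10(1 − q), and the SD is that of the mixture.

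| Not operated | Difference, all randomised | Power, all randomised | Power, operated only |
|---|---|---|---|
| 5% | 9.5 | 0.82 | 0.85 |
| 10% | 9.0 | 0.77 | 0.83 |
| 20% | 8.0 | 0.67 | 0.79 |

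Worked line for 10%: the arm means are 27 and 18. The variances are 0.9 × 1300 − 27² = 441 and 0.9 × 800 − 18² = 396, so the average SD is √418.5 = 20.5. Then 9/(20.5 × √(2/76)) = 2.71, and power is Φ(2.71 − 1.96), about 0.77.

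**The case against.** A reader might infer that the protocol turns its intention-to-treat analysis into an operated-only one, with endovascular switches, ruptures, cancellations and deaths all dropped. The article does not support that.

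- No section says that any of these participants are removed, and section 3.1 says the opposite.
- Endovascular switches and ruptures that reach surgery are admitted and can have a CCI.
- Death is already 100 on the scale, so a preoperative death could be scored.
- The wording in section 3.5.1 describes when selection begins. It does not say how certain open repair is at randomisation. Section 3.3.1 requires participants to be waiting for planned open repair, and section 3.5.2 randomises only once eligibility is confirmed.
- A 20% dropout allowance is routine planning and does not define the analysis set.
- Ruptured, symptomatic and large aneurysms are excluded, no serious exercise-related events are expected, and balanced deaths nearly cancel.
- Rules for missing outcomes often sit in an analysis plan, which is not shown here.

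All of this stands against the stronger reading. It does not remove the narrower point. An analysis plan can decide how to handle recorded events, but it cannot recover events that nobody was told to collect over a defined window for participants never admitted. The exclusion in section 3.7 is also a statement in the protocol, not a gap in it. Exclusion from participation need not mean exclusion from analysis, but the article does not say which is meant.

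**Conclusion.** The point holds in limited form. The article promises a primary analysis of everyone randomised, but assures a CCI only for those who reach the surgical admission. Deaths before admission, cancellations and post-randomisation exclusions are left without a stated value, and the exclusions can be unbalanced by design.

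The likely size is unknown, because the article gives no rate of preoperative death or of participants not operated on. Under the stated assumptions, one to three unbalanced deaths move an arm's mean by 0.9 to 2.8 points. That is worth settling in advance but is not evidence that the result will be biased. The power figures in step 4 likewise rest on assumed means and assumed shares not operated.

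**What to change.** Reconcile sections 3.1, 3.5.6, 3.6.2 and 3.7, preferably before the interim look at the primary outcome:

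1. State that participants excluded from the intervention after an event remain in follow-up and in the primary analysis by assigned arm. This leaves the clinical rule on stopping training untouched.
2. Fix the start and end of the CCI window, and align the 45 days with the recording during admission.
3. Score any death from randomisation to the end of that window as 100.
4. Count complications of whichever aneurysm repair is done.
5. For participants not operated on, take events from hospital records over a defined window.
6. Report the operated-only (open repair) comparison as a sensitivity analysis.
7. Qualify the stated power for the expected share not operated.

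The practical cost is an amendment and a chart review, using the kind of hospital records that section 3.5.8 already consults. The statistical cost is dilution. Unoperated survivors with low scores pull the arms together, and power under the step 4 assumptions falls to about 0.82, 0.77 and 0.67 at 5%, 10% and 20% not operated. If a sizeable share is expected, that loss is not trivial and should be stated openly.
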